## Abstract

**Background:**

Major depressive and anxiety disorders affect 61 million adults in the United States. People living with mental illness, including depression and anxiety, experience stigma associated with the illness and receiving treatment for their illness. Stigma refers to negative attitudes or beliefs about mental illness or negative behaviors directed toward persons with mental illness. Stigma is a leading and fundamental cause of health inequities. Contact interventions, which are premised on the idea that positive and voluntary contact with persons with mental illness can effectively reduce mental illness stigma, are aimed at reducing stigma and improving health outcomes. Video-based interventions improve knowledge, attitudes, and behavior in the short term, and there is a need for randomized controlled trials of indirect contact or video-based contact interventions to address stigma and engagement in mental health services.

**Objective:**

The aim is to assess the feasibility and acceptability and test the preliminary efficacy of a self-administered video-based mobile app in reducing mental illness stigma among Black adults with moderate to severe depression or anxiety.

**Methods:**

The intervention will involve short videos (6-12 minutes in length) of patients describing personal narratives of mental illness, treatment, and recovery and will be delivered over 4 weeks, with 2 booster sessions in weeks 6 and 12. Study participants (N=90) will be randomly assigned to 1 of 3 treatment arms: a standard video-based app (n=30), a video-based app modified with a concordant patient video (n=30), and a waitlist control (n=30).

**Results:**

We hypothesize the concordant and standard intervention group will have greater mental health service use, lower stigma, and lower mistrust compared to the waitlist arm. As a feasibility study, we will pilot the outcome analyses (to detect a signal and estimate direction of analysis). On the basis of the sample size of 90 (n=30 in each treated group and control group) and power at 72%, we will be able to detect a medium effect size of Cohen *d*=0.49 at α=.05 for comparing the intervention versus control proportions for any engagement in mental health care services.

**Conclusions:**

Given the low uptake of mental health services for people experiencing early signs and emerging symptoms of mental illness, efforts to increase early access to mental health services will be met with ongoing substantial barriers to mental health care use if stigma and medical mistrust are left unaddressed. Data from this pilot and feasibility randomized controlled trial will provide critical information about the feasibility and acceptability of this intervention and preliminary efficacy estimates. This study will fill a critical public health gap created by the stigma that leads to delayed diagnosis, delayed entry into mental health treatment, and increased morbidity and mortality related to mental illness.

**Trial Registration:**

ClinicalTrials.gov NCT06316804; https://clinicaltrials.gov/study/NCT06316804

**International Registered Report Identifier (IRRID):**

DERR1-10.2196/81645

## Introduction

### Background

Major depressive and anxiety disorders affect 61 million adults in the United States [1-3]. People living with mental illness, including depression and anxiety, experience stigma associated with the illness and receiving treatment for their illness [4,5]. Stigma, which refers to negative attitudes or beliefs about mental illness or negative behaviors directed toward persons with mental illness [6,7], is a leading and fundamental cause of health inequities [8-10]. The primary mechanisms through which stigma worsens mental health outcomes include delayed treatment seeking and limited access to care [4,11]. Contact interventions, which are premised on the idea that positive and voluntary contact with persons with mental illness can effectively reduce mental illness stigma [9,11,12], are aimed at reducing stigma and improving health outcomes. Past studies show face-to-face contact is superior to video-based contact; however, more recent randomized controlled trials (RCTs) show that video-based contact has a comparable effect in reducing stigma [4,7,13-16]. Video-based interventions improve knowledge, attitudes, and behavior in the short term, and there is a need for RCTs of indirect contact or video-based contact interventions to address stigma and engagement in mental health services [4,7,15,16].

Interventions to reduce mental illness stigma among Black adults remain understudied [4,17-19], and the role of mistrust is rarely examined [20]. There is a need for methodologically strong research to develop scalable interventions to reduce stigma and address medical mistrust, thus potentially increasing mental health service use [4,15,21]. Concomitant with these known gaps in the current literature, we developed iteratively and using a co-design user-centered design model, a mobile intervention platform to reduce stigma, address medical mistrust, and increase mental health service engagement among Black adults. In this study protocol manuscript, we present on the planned protocol for a novel randomized controlled intervention, testing the feasibility and acceptability of an antistigma mental health intervention delivered remotely on a digital mental health platform.

Several forms of stigma are prominent among persons with mental illness and contribute to increased psychological distress [8,9,11,22-24]: enacted stigma—the behavioral manifestations of negative attitudes about persons with mental illness, including stereotyping, social distancing, prejudice, and discrimination [25,26]; anticipated stigma—the expectation that one will be devalued for having mental illness and/or being subjected to stereotyping, prejudice, or discrimination if one’s mental illness were to become known by others [8,27-29]; and internalized stigma—endorsing the negative attitudes and beliefs as valid, thereby developing self-defacing beliefs about oneself [28,29]. Among Black adults, the content of mental health stigma includes beliefs that mental illness is attributed to a lack of faith in God, weakness, or lack of self-control [30-33]. However, current research studies approach Black adults as a homogenous group, and this assumption of homogeneity limits the efficacy of programs that seek to reduce mental illness stigma among Black adults in the United States [34-37]. Previous studies show that concordance in sociodemographic factors including race, ethnicity, and religiosity may improve the acceptability and efficacy of antistigma contact interventions [33].

Mobile mental health apps offer a mechanism to deliver interventions that can be modified in real time to align with user characteristics (such as race, ethnicity, or religious background) [38-42]. The largest systematic reviews and meta-analysis on stigma interventions to date have called for more culturally informed approaches to the design of stigma interventions [4,6,15,19,43]. In addition, concordance (eg, in race or ethnicity) between patients and providers is associated with higher trust, improved communication, and higher intent to adhere to health services [44-46]. Medical mistrust may be directed toward health professionals or health systems and is a known barrier to engagement in mental health services for the Black population [20,47,48]. Antistigma interventions that simultaneously address medical mistrust may have enhanced efficacy [20,49-51]. Previous studies show that having health professionals of shared racial, ethnic, or religious backgrounds would reduce their hesitancy toward accessing mental health services [46,52,53].

### Study Objective

The main study objective is to address mental health gaps around the role of stigma in reducing mental health service engagement by assessing a mobile app, codeveloped with end users. The user-centered design phase involved usability testing to refine intervention components to meet the needs and preferences of end users through an iterative, stepwise design process. Given the high stigma among underserved populations including Black adults with mental illness, screened participants in the user-centered design study reported a preference for key informant interviews over focus groups. A separate paper has been published on the app development of the intervention that is being tested and reported on in this protocol study manuscript. This paper describes the protocol for a 3-arm randomized controlled waitlist trial to assess the feasibility and preliminary efficacy of an antistigma mobile mental health app, which integrates components that address the mistrust of health systems, in reducing mental illness stigma among Black adults with moderate to severe depression or anxiety.

### Conceptual Framework

The conceptual model for stigma reduction is based on well-established sociological and psychological theories of behavior change. This model predicts that positive and voluntary contact with people living with mental illness can effectively reduce stigmatizing attitudes and stigmatizing behaviors [9,12,13]. On the basis of extensive research conducted by Corrigan et al [6], successful contact interventions have the following characteristics: targeted (ie, at a specific outcome, such as the use of mental health services); local (within a geographical region such as an urban setting); credible (ie, to the target group); continuously delivered (ie, not a single point of contact); and involves contact (closing the social gap between people with stigma and people living with mental illness through direct [in person] or indirect [video based or virtual] means).

Meta-analyses have consistently shown that both face-to-face and video-based contact with people living with mental illness can reduce stigma. In contrast to video-based contact, face-to-face interventions require intensive professional or peer facilitators, which significantly limits scaling, dissemination, and implementation goals [7,54,55]. The delivery of face-to-face stigma-reducing interventions can potentially be addressed by use of mobile mental health technology to deliver video-based interventions. Recent RCTs of interventions that optimize the core underpinnings of video contact show that video-based contact has similar efficacy as face-to-face contact [7,14,55-57].

## Methods

### Hypotheses

We hypothesize the concordant and standard intervention group will have greater mental health service use, lower stigma, and lower mistrust compared to the waitlist arm. We also hypothesize that among the two intervention groups, the concordant intervention group will have greater effects on the primary and secondary outcomes compared to the standard intervention group.

### Study Design and Setting

The study follows a single blind design among 2 experimental arms and 1 waitlist control arm. Participants are unaware of which intervention arm they are assigned among the two experimental arms. It was not feasible to fully blind the participants to the intervention versus waitlist arms, but we are able to blind participants to the specific content of the two intervention arms.

The intervention will involve short videos (6-12 minutes in length) of patients describing personal narratives of mental illness, treatment, and recovery and will be delivered over 4 weeks, with 2 booster sessions in weeks 6 and 12. Study participants (N=90) will be randomly assigned to 1 of 3 arms: a standard video-based app (n=30), a video-based app modified with a concordant patient video (n=30), and a waitlist control (n=30).

The study team used the SPIRIT (Standard Protocol Items: Recommendations for Interventional Trials) checklist in the development of the study protocol and conceptualization of the study and as study activities were initiated. We have included the page reference numbers for the SPIRIT checklist. The study team will follow the CONSORT (Consolidated Standards of Reporting Trails) checklist criteria throughout the study, including randomization scheme, study procedures, and planned analysis.

### Intervention Overview

#### Intervention Format

This study consists of a self-administered video-based stigma reduction app using an RCT design among Black adults (ages 18-45 years) from diverse ethnic backgrounds with moderate to severe depression and/or anxiety (9-item Patient Health Questionnaire ³10 or 7-item generalized anxiety disorder ³10) who have not accessed mental health services in the past year.

The intervention videos involve 6- to 12-minute videos, offering narratives on treatment and recovery by people living with mental illness from diverse backgrounds including narratives of depression illness and recovery [58,59]. In the adapted (concordant) intervention arm, participants will be offered video content from someone with the same or similar sociodemographic background based on their reported characteristics at screening [60]. The standard (discordant) intervention arm will involve video content from someone from a different sociodemographic background. The 2 intervention conditions will be delivered on a secure HIPAA (Health Insurance Portability and Accountability Act)-compliant platform. Content will be available in English at an eighth-grade reading level [61,62]. New sessions will be prompted each week based on the experimental condition arm, and usage data will be collected. The study will include individuals from various age groups, education and income levels, and gender identities. Study participants will be randomly assigned to 1 of 3 arms: a standard video-based app (n=30), a video-based app modified with a concordant individual (n=30), and a waitlist control (n=30).

#### Setting, Participants, and Eligibility Criteria

Recruitment will take place through the Massachusetts General Hospital patient registry, online social media advertising, and in partnership with community-based organizations. All participants will be prescreened via a phone call and/or an online form. All participants will complete an orientation call prior to randomization. To ensure representativeness of the sample, we will use a stratified random sampling of study participants to include equitable numbers of genders, migrant status, and ethnic origin (African Americans, African immigrants, Afro-Caribbean immigrants, and Afro-Latina). The participant eligibility criteria are shown in Textbox 1.

Participant eligibility criteria.
**Inclusion criteria**
Black adults with moderate to severe depression (9-item Patient Health Questionnaire ³10) or anxiety (7-item generalized anxiety disorder ³10) who are not receiving routine mental health careAged 18 to 45 years at time of screening. This age range was chosen due to variability in technology across age groups, reducing the heterogeneity of technology use among participants.English speakingOwn a smartphone and have internet access
**Exclusion criteria**
Visual, hearing, voice, or motor impairments that would prevent engagement in study proceduresDiagnosis of psychotic disorder or severe suicidality for which participation would be inappropriate

Language variance and lack of access to a smartphone would prevent engagement in study procedures and impact feasibility assessment.

#### Procedure

At the initial visit, we will obtain baseline measurements of enacted, anticipated, and internalized stigma [8]. The self-administered intervention will be delivered over 4 weeks based on the experimental condition, and participants will each receive a standard video-based intervention or a concordant video-based intervention. Each week, participants will be prompted with a notification (via SMS text message and/or email) to access that week’s intervention components. The content of booster sessions in weeks 6 and 12 will be based on the experimental arm and will contain repeat sessions used in each experimental arm. The waitlist arm will receive the concordant video condition after 12 months. At the orientation visit, for all participants, guidance on obtaining emergent or urgent services is provided, including reaching out to the study team (which includes a social worker, resource specialist, and psychiatrist) at any time.

#### Recruitment

Patients who present for general medical care at the selected Mass General Brigham community clinic partners are routinely given screening tests (9-item Patient Health Questionnaire and 7-item generalized anxiety disorder). The community advisory board will support recruitment efforts. Flyers and announcements will be available in clinics and shared with community partners. Any participant who meets the entry criteria on screening tests and who may have declined mental health services will be offered the stigma intervention program. If a patient agrees to participate, a trained research assistant will contact the patient. In addition, using the electronic medical records, patients who meet the criteria within the last 12 months and have not received mental health services in the past year will be invited to participate in the eligibility screening. The waitlist arm will receive holiday cards and text reminders to complete assessments. Incentives to participate in the stigma intervention include offering a low intensity, nonjudgmental, and confidential option to patients who have screened positive for depression or anxiety but who are not receiving routine mental health care. To manage attrition in app use, which is common, we will send out weekly reminders using multiple methods such as email, text, and phone call reminders for participants missing study activities or assessments.

#### Assessments

Study recruitment and retention rates will be assessed to determine the feasibility of study procedures (Table 1). The feasibility outcomes will be measured based on acceptability of the study through measures of usability: System Usability Scale (SUS) and usefulness, satisfaction, and ease of use (USE) scales [63,64]. We will also document adherence based on time spent on the intervention program and app use data to assess the completion of video activities. Assessments will be completed using standardized measures (Table 1).

**Table 1 table1:** Intervention feasibility trial process and outcomes.

Domain, construct, and measure				Baseline		Each week		After the booster		Follow-up at 6-12 months
**Feasibility outcomes**										
	**Acceptability**									
		USE^a^ and SUS^b^			✓		✓		✓	
	**Retention to intervention**									
		Completed assessments			✓		✓		✓	
	**Adherence to intervention**									
		App metrics			✓		✓		✓	
**Primary outcomes**										
	**Demographic**									
		Survey	✓							
	**Any engagement with mental health services**									
		EMR^c^	✓						✓	
**Secondary outcomes**										
	**Sigma scores**									
		RIBS^d^ and ISMI^e^	✓		✓		✓		✓	
	**Help-seeking behavior**									
		GHSQ^f^	✓		✓		✓		✓	
	**Medical mistrust scores**									
		GBMMS^g^	✓		✓		✓		✓	
**Targets**										
	**Sigma and medical mistrusts**									
		RIBS, ISMI, and GBMMS	✓		✓		✓		✓	

^a^USE: usefulness, satisfaction, and ease of use.

^b^SUS: System Usability Scale.

^c^EMR: electronic medical record.

^d^RIBS: Reported and Intended Behavior Scale.

^e^ISMI: Internalized Stigma of Mental Illness.

^f^GHSQ: General Help-Seeking Questionnaire.

^g^GBMMS: Group-Based Medical Mistrust Scale.

#### Data Analysis and Power Calculation

As a feasibility study, we will pilot the outcome analyses (to detect a signal and estimate direction of analysis), recognizing that the trial may be underpowered. On the basis of the sample size of 90 (n=30 in each treated group and control group) and power at 72%, we will be able to detect a medium effect size of Cohen *d*=0.49 at α=.05 comparing the intervention versus control proportions for any engagement in mental health care services.

For the continuous outcomes (such as Group-Based Medical Mistrust Scale), we will use generalized linear mixed models with a gamma distribution for continuous outcomes. If variables are not normally distributed, we will explore a transformation. For binary outcomes, we will use Poisson or negative binomial regression depending on the variance.

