### Randomization and Blinding

#### Randomization Scheme

Participants will be randomized to 1 of 3 arms: a standard video contact arm, a concordant video contact arm, and a waitlist control arm as outlined in our CONSORT diagram (Figure 1). Assignment to the 3 arms in a 1:1:1 allocation ratio will be determined centrally by the principal investigator according to a computer-generated random schedule (ie, in Stata [StataCorp]). There is no practical way to fully blind the study participants to treatment assignment versus waitlist and accomplish the objectives of the study. To avoid bias among participants receiving the concordant or standard video assignment, we will conceal treatment arm allocation. We are testing the salience of concordance across sociodemographic characteristics; unblinding would prevent unbiased testing of the role of concordance. The study participants will be blinded to the two intervention arms and will be unaware which intervention arm they were assigned throughout the study. The research study staff and biostatistician (who will be conducting the outcome assessments and analysis, respectively) will be blinded to treatment assignment status. The participants assigned to the waitlist will receive access to the concordant video contact intervention after they have completed their 12-month study assessment. To avert chance imbalances by ethnicity and sex, we will stratify randomization by ethnicity (African American, Afro-Caribbean or Afro-Latino, and African immigrant) and sex. The regression models for the primary analysis include the stratification variables as covariates to ensure the estimated standard errors are accurate. We hypothesize that the concordant video arm will be superior to the standard video arm. The standard video arm is needed to test our hypothesis and understand the mechanistic effect of each therapeutic target.

Reliability and validity data for the study assessments are shown in Table 2 [65-68].

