#### Planned and Interim Analysis

We hypothesize that the contact-based intervention arm that incorporates an approach using concordance will reduce stigma and lower medical mistrust, improving engagement in mental health services. Feasibility will be assessed by meeting our recruitment goals (90 participants), obtaining 80% of follow-up self-report data, and having a dropout rate of <20% in one or more treatment conditions, which is in line with previous mobile mental health intervention RCTs [69] and which would indicate the treatment format for future research. Recruitment and retention rates, acceptability, adherence to study, and treatment will be reported as percentages. The average USE and SUS scores will be reported.

We will assess the moderating role of sociodemographic factors (religiosity, migrant status, and socioeconomic status) by controlling for these variables in our pre-post assessments.

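### The 72% power stated for Cohen d=0.49 names no test side, contrast or event rates; a two-sided 5% test at this size gives about 47% (one arm v waitlist) or 59% (arms pooled)

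*Protocol article*

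**What the plan says.** The methods section on data analysis and power states "On the basis of the sample size of 90 (n=30 in each treated group and control group) and power at 72"%, the trial can detect "a medium effect size of Cohen *d*=0.49 at α=.05 comparing the intervention versus control proportions" for any engagement in care. The abstract's Results paragraph repeats the statement, again for "comparing the intervention versus control proportions for any engagement in mental health care services".

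The elements around that figure are these:

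- **Allocation** (Randomization Scheme): "Assignment to the 3 arms in a 1:1:1 allocation ratio", so 30 per arm.
- **Hypothesis** (Hypotheses): directional. "We hypothesize the concordant and standard intervention group will have greater mental health service use" than the waitlist arm. A second hypothesis places the concordant arm above the standard arm.
- **Caveat**: the methods section introduces the figure by "recognizing that the trial may be underpowered". Limitations and Conclusions say the same in stronger terms. The abstract's power sentence carries no such caveat, although it does call the study a feasibility study.
- **Dropout** (Planned and Interim Analysis): one feasibility criterion is "having a dropout rate of <20% in one or more treatment conditions".

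The article does not say whether α=.05 is one-sided or two-sided, whether the two intervention arms are pooled for the comparison, what engagement rate is expected in any arm, or whether the power figure allows for loss.

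**The concern.** A reader given d, α and the arm sizes should be able to recover the power. Here the usual reading, a two-sided 5% test, does not return 72% for either contrast that the design offers. The figure can be approached only by choosing a side and a contrast that the text does not declare.

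The effect size is also on the wrong scale. Cohen d is a standardised difference in means, whereas the primary outcome is yes/no. Without a control rate, 0.49 cannot be turned into a difference in engagement.

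This is the article's only power statement. It is attached to the primary outcome, it appears in the abstract, and the pilot is meant to inform a fully powered trial. Someone planning that trial, or reading a null result here, could take 72% as the power of each arm against waitlist.

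**Working it through.** **Inputs.** d=0.49, α=.05, 30 per arm and stated power 72% come from the power paragraph; 1:1:1 allocation comes from the randomization section. Test side and contrast are not stated, so both options of each are tried.

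**Formula (normal approximation).** Noncentrality λ = d × √[n₁n₂/(n₁+n₂)]; power = Φ(λ − z), with z = 1.960 two-sided or 1.645 one-sided.

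- 30 v 30: λ = 0.49 × √15 = 1.898
- 60 v 30: λ = 0.49 × √20 = 2.191

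**Attempt to reproduce 72%** (noncentral t in brackets):

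| Contrast | Two-sided .05 | One-sided .05 |
|---|---|---|
| One arm v waitlist, 30 v 30 | Φ(−0.062) = 47.5% (46.3%) | Φ(0.253) = 60.0% (59.1%) |
| Both arms v waitlist, 60 v 30 | Φ(0.231) = 59.2% (58.2%) | Φ(0.547) = 70.8% (70.2%) |

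Only the bottom right cell is within 2 points of 72%. An even split of 90 into 45 v 45, which is not this design, gives 64.2% two-sided and 75.2% one-sided.

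**Effect that 72% power corresponds to.** d = (z + 0.583)/√[n₁n₂/(n₁+n₂)].

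- Two-sided: 2.543/√15 = 0.66 (30 v 30); 2.543/√20 = 0.57 (60 v 30)
- One-sided: 2.228/√15 = 0.58 (30 v 30); 2.228/√20 = 0.50 (60 v 30)

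At d=0.49, 72% two-sided power would need about 54 per arm for one arm against waitlist.

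**Reading 0.49 on a proportion scale.** As Cohen h, p₂ = sin²(arcsin√p₁ + 0.245). A control rate of 20% then pairs with 42%, and 30% with 54%. These control rates are assumptions, as the article gives none. The two-proportion formula over assumed control rates from 5% to 50% gives:

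- 30 v 30, two-sided: 44–47%
- 60 v 30, two-sided: 49–60%
- 30 v 30, one-sided: 57–60%
- 60 v 30, one-sided: 64–71%

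Converting d to an odds ratio, exp(0.49 × π/√3) = 2.43, gives less: over the same rates, pooled power is 13–50% two-sided and at most 63% one-sided.

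**Sensitivity to loss (an assumption).** If 20% of primary outcomes were lost:

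- 24 v 24: λ = 0.49 × √12 = 1.697, power about 40% two-sided and 52% one-sided
- 48 v 24: λ = 0.49 × √16 = 1.960, power about 50% two-sided and 62% one-sided

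**The case against.** The strongest reply is that the text never says two-sided. Its hypotheses are directional, and setting the intervention against control can naturally mean both arms pooled. On that reading power is 70–71% and 72% corresponds to d of about 0.50, so the printed figure is nearly right. This stands in part. A reader might infer that 72% is simply an arithmetic error, and the document does not support that: it leaves open the one reading under which the figure roughly holds. But a directional hypothesis does not declare a one-sided test, an unqualified α=.05 is ordinarily read as two-sided, and pooling is not stated either.

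A second reply is that 72% may come from a method not shown. Averaging four repeated assessments would give 72% two-sided if their correlation were about 0.41 (30 v 30) or 0.65 (60 v 30). Those correlations are invented, and nothing in the power paragraph points to such a method. A three-group chi-square test with w=0.3 and N=90 also gives 72.3%, but that is a different effect measure and not an intervention-versus-control comparison. Neither matches the sentence as printed.

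Third, the harm is limited. A reader might infer that the article oversells its power or that N=90 must rise. Neither is supported: the methods, limitations and conclusions all acknowledge low power, and 90 is a feasibility recruitment goal that nothing shows was derived from this figure. This stands, and it lowers the severity.

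Fourth, a reader might infer that the power must be discounted for 20% dropout. The criterion is a feasibility threshold, not a power input, and the primary outcome can be drawn from medical records even if app assessments are missed. This also stands, so loss belongs only in a labelled sensitivity figure.

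Finally, the power sentence does not cover concordant versus standard. That is correct. It follows only that 72% should not be carried over to that 30 v 30 comparison.

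**Conclusion.** The point holds as an incompletely specified power statement whose figure is not met under the ordinary reading. Two-sided at 5%, the design gives about 47% for one arm against waitlist and about 59% for the arms pooled, some 25 and 13 points below 72%. The figure is approached (70–71%) only by a one-sided pooled test with complete follow-up, none of which is declared. For either arm alone against waitlist, no simple two-group test at 5% reaches it; the best is 60%, one-sided.

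These results assume a single unadjusted two-group comparison and treat 0.49 as d or as h. The detectable difference in engagement cannot be recovered from the article without assuming a control rate. Severity is moderate: a printed figure on the primary outcome needs correcting, in a document that already says the trial is underpowered.

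**What to change.** Keep N=90 and restate the sentence in both the abstract's Results paragraph and the power paragraph of the methods:

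1. Name the contrast and the side of the test.
2. Replace Cohen d by two proportions, or by Cohen h with an assumed control rate.
3. Correct the power to match.

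Possible wording: *With a two-sided α of .05, both intervention arms pooled against waitlist (60 v 30) give about 58–59% power for Cohen h=0.49, for example 30% v 54% engagement (control rate assumed); each arm alone against waitlist (30 v 30) gives about 47%.*

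If a one-sided pooled test was intended, say so and state about 70–71%. Optionally add a sensitivity figure for 20% loss of the primary outcome (two-sided: about 50% pooled, 40% single arm), labelled as an assumption.

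The cost is wording only. No participants are added; the stated power becomes less favourable if the test is two-sided.
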